#### 4 TRIAL DESIGN

This study is an exploratory, dose-escalating pilot trial to test the feasibility, safety and preliminary efficacy of aerosolized lung delivery of surfactant, a medicine with a known safety profile, to improve the oxygenation and pulmonary compliance of adult patients diagnosed with moderate to severe COVID-19 associated lung injury with increasing oxygenation requirements.

The timing of escalating dosing and assessment of clinical response is based on the rapid oxygenation response of infants with surfactant deficiency ([Collaborative European Multicenter Study Group 1988](#)) and the clinical response described in adults after endobronchial administration of surfactant in ARDS ([Walmrath 2002](#)). Nevertheless, it is acknowledged that the optimal dose required for surfactant replacement therapy in adults and the rate of clinical response in patients with COVID-19 are unknown. Therefore, we propose a dose-escalating, adaptive trial design in which the feasibility of administration of aerosolized surfactant and the clinical response in mechanically ventilated COVID-19 patients are assessed. The dosing regimen may be adjusted based on accumulating data and may depend on the dose required to achieve a clinical response and the speed with which that response is seen.

Patients will enter the study and will be randomised to 3:2 for the treatment and control arms where they will receive three doses of Alveofact® via nebulizer or the control arm where treatment will follow standard of care.

Patients in the treatment arm will be assigned into cohorts sequentially as follows:

- **COHORT 1:** 3 patients will receive 10 vials (1080 mg) each of Alveofact® at dosing times of 0 hours, 8 hours and 24 hours. 2 controls.

- **COHORT 2:** 3 patients will receive 10 vials (1080 mg) of Alveofact® at dosing times of 0 hours and 8 hours, and 30 vials (3240 mg) of Alveofact® at a dosing time of 24 hours. 2 controls
- **COHORT 3:** 3 patients will receive 10 vials (1080 mg) of Alveofact® at a dosing time of 0 hours, and 30 vials (3240 mg) of Alveofact® at dosing times of 8 hours and 24 hours. 2 controls
- **COHORT 4:** 3 patients will receive 30 (3240 mg) vials each of Alveofact® at dosing times of 0 hours, 8 hours and 24 hours. 2 controls

Control arm:

**CONTROL:** Each cohort of 3 patients (in the treatment arm) will have 2 patients acting as controls (5 patients per cohort; total control n=8). The protocol for the control arm will be identical to the treatment arm except for surfactant nebulization.

After each cohort has completed treatment (or equivalent time for controls), the investigators will pause to review the outcomes of the treatment based on the co-primary outcomes (PaO2/FiO2 ratio and Ventilation index at 48 hours), reported adverse events and any additional safety or feasibility considerations. Additional trial outcome data may be taken into account if considered important in the opinion of the principal and chief investigators or if requested by the DSMB or TSC.

The decision to progress may be: 1. increase dose to next cohort level according to planned schedule (see below); 2. decrease dose to previous cohort level according to planned schedule (see below); 3. decrease dose to alternative level (specifically for cohort 1); 4. maintain dosage at current level. If there is a substantial and sustained improvement in the outcomes of a cohort, the subsequent cohorts may continue with the same dose as the previous cohort. If no improvement is observed, the subsequent cohort may increase the dosage. Early and substantial improvement during administration of the drug, or adverse events thought to be a safety concern, may prompt the investigators to reduce the administered dose during the conduct of the study.

Decisions relating to trial progression and dose escalation/maintenance/reduction will be made by the TSC after review of data by the DSMB. The DSMB will meet immediately prior to the TSC in open session but may meet in closed session at the request of any members of the DSMB or TSC. The TSC will meet after the DSMB and receive a verbal update from the DSMB. The TSC will be the final arbiter of trial progression and dose escalation/maintenance/reduction decisions. The majority of the TSC and all members of the DSMB will be independent of the trial investigators and trial conduct. An extraordinary meeting of the DSMB may be convened if the investigators have any safety concerns. Such a meeting would make recommendations to the TSC on trial continuation/discontinuation. The trial will not be discontinued on the basis of lack of efficacy. The trial may be stopped early on the basis of safety or feasibility concerns.

[figure not shown]

## 5 TRIAL SETTING

This is a multicentre, randomised, open-label clinical trial conducted at University Hospital Southampton NHS Foundation Trust and University College London Hospital NHS Foundation Trust. Adult patients diagnosed with severe COVID-19 associated lung injury with increasing oxygenation requirements will be recruited to the study from each site's inpatient population.

## 6 PARTICIPANT ELIGIBILITY CRITERIA

### 6.1 Inclusion criteria

1. Age  $\geq 18$  years old
2. Confirmed COVID-19 positive by PCR
3. Within 24 hours of mechanical ventilation
4. Assent obtained from personnel legal representative (PerLR) or professional legal representative (ProfLR)

### 6.2 Exclusion criteria

1. Imminent expected death within 24 hours
2. Specific contraindications to surfactant administration (e.g. known allergy, pneumothorax, pulmonary hemorrhage)

3. Known or suspected pregnancy
4. Stage 4 severe chronic kidney disease or requiring dialysis (i.e., eGFR < 30)
5. Liver failure (Child-Pugh Class C)
6. Anticipated transfer to another hospital, which is not a study site within 72 hours
7. Current participation or participation in another study within the last month that in the opinion of the investigator would prevent enrollment for safety purposes
8. Consent declined

## **7 TRIAL PROCEDURES**

### **7.1 Recruitment**

#### **7.1.1 Participant identification**

Hospitalised patients aged  $\geq 18$  that require endotracheal intubation will be considered for inclusion in the study.

Potential patients will be identified by an existing member of the patient's clinical care team. Participant medical records will be reviewed for consideration of inclusion / exclusion criteria. A delegated investigator will confirm inclusion / exclusion prior to enrolling a patient on the study.

#### **7.1.2 Screening**

Study participants will be hospitalised patients aged  $\geq 18$  with laboratory-confirmed SARS-CoV-2. The investigator or delegate will review the patient's medical history and medical notes for the inclusion and exclusion criteria (section 6.1 and 6.2).

Pregnancy is an exclusion criterion. Non-pregnant status will be confirmed via urine pregnancy test at screening if this has not been carried out as part of standard of care already.

#### **7.1.3 Payment**

No payment will be made to participants.

### **7.2 Consent**

It is the responsibility of the Principal Investigator or co-investigator (where the responsibility has been delegated by the Principal Investigator as captured on the Site Signature and Delegation Log) to obtain informed consent/eConsent for each patient before performing any trial related procedure.

It is not expected that patients considered for enrollment in this study will have the capacity to consent to take part due to the nature of the underlying disease process, as they will be under sedation and will be mechanically ventilated. As a result of this, the study information sheet will be made available to a personal legal representative (PerLR);

The personal legal representative will be fully informed of all aspects of the trial and the potential risks. The following will be emphasised:

- Participation in the study is entirely voluntary.
- Refusal to participate involves no penalty or loss of medical benefits.
- The patient may withdraw from the study at any time.
- The personal legal representative is free to ask questions at any time to allow him or her to understand the purpose of the study and the procedures involved.
- There may be no direct benefit from participation.

- The aims of the study and all tests to be carried out will be explained. The personal legal representative will be given the opportunity to ask about details of the trial and will then have time to consider whether to participate or not.
- The risks of participating in the study will be fully explained.

If the personal legal representative decides that they wish for the patient to participate, they will sign and date the legal representative declaration form and will be given a copy. The original legal representative declaration form will be stored as source documentation. These forms will also be signed and dated by the Investigator.

In cases where it is not possible for a personal legal representative to be present in the hospital due to local visitor restrictions, the study can be discussed with the patient's personal legal representative over the telephone. A copy of the legal representative declaration form can be sent to the personal legal representative via email or online declaration form and returned to the study team.

There will also be an option for the personal legal representative to give assent electronically via a secure website. The telephone discussion will be documented in the patient's medical notes alongside a copy of the legal representative declaration form.

A professional legal representative (usually a consultant not directly involved in the study) will be asked to counter sign the legal representative telephone declaration form in situations where personal legal representative assent has taken place remotely and it has not been possible for the declaration form to be completed and signed by the personal legal representative.

COVID-19 patients intubated are at risk of rapid deterioration and given the urgent need to initiate treatment on the patients and the potential benefit of starting the treatment within 24 hours after intubating. If it is not possible to approach a personal legal representative for assent, a professional legal representative will decide regarding study participation on the patient's behalf. If the professional legal representative agrees for the patient to take part, they will sign a professional legal representative declaration form; the form will also be signed by a member of the study team (delegated by PI to take consent). The discussion will be documented in the patient's medical notes alongside a copy of the professional legal representative declaration form.

Personal or professional legal representative will be given sufficient time to review the information provided and ask questions before signing the assent / declaration form. Only members of the research team who have undergone the appropriate GCP training will be able to seek agreement from potential patients' personal or professional legal representative.

Once participants have regained capacity, they will be asked to consent to their continued participation in the study. The study rationale and conduct will be explained to them outlining any interventions which have already been undertaken as well as those that are still required.

Details of the informed consent or assent discussion will be recorded in the patient's medical record. This will include the date consent was given, with the name of the trial and the version number of the Participant Information Sheet and Informed Consent Form. Throughout the trial the patient or personal legal representative should have the opportunity to ask questions about the trial and any new information that may be relevant to the patient's continued participation should be shared with them in a timeously. On occasion, it may be necessary to re-consent the patient or personal / professional legal representative, for example if new information becomes available or an amendment is made to the protocol that might affect the patient's participation in the trial. In this case the process above will be followed and the patient's right to withdraw from the trial respected.

A flow chart summarizing the consent and assent processes is included below.

### **Assent and consent flow chart**

[figure not shown]

### 7.2.1 Additional consent provisions for collection and use of participant data and biological specimens in ancillary studies, if applicable

Participants will be asked to consent for the use of their samples in future research. Consent for this is optional. If the participant chooses not to consent to this their samples will be destroyed at the end of the study. Any samples stored for future research will be anonymised. Should a participant choose to withdraw from the study prior to completion, they will be able to withdraw their consent for their samples to be stored and the samples will then be destroyed.

### 7.3 The randomisation scheme

Patients will be randomised to 3:2 for the treatment and control arms using ALEA Randomisation. ALEA Randomisation is an internet-based service provided by FormsVision BV that supports online patient registration and randomisation and is fully integrated with ALEA eCRF. ALEA Randomisation has been built as a series of components, in order to support interoperability and customised extensions. The components make use of a common standard representation of data and metadata: The Operational Data Model of CDISC. Within ALEA Randomisation, the components share a database for storing and retrieving information about the trial, and a separate database for storing and retrieving patient data. ALEA Randomisation supports the following methods of randomisation for healthcare trials. It supports trials with any number of treatment groups, and randomisation ratios other than 1:1. In this study we will be using the block randomisation schema.

The following series of numbers will comprise the subject identifier:

- Three alpha characters – site code – UHS and UCH
- 2-digit subject number (e.g. 03)

Will be allocated by the site, reflecting the order of consent to the study within the site. For example, the third subject who signed an informed consent form at study UHS will be identified as Subject UHS-03.

The enrolment number will be added to the consent form at the site.

### 7.4 Blinding

N/A. This is an open-label study.

### 7.5 Baseline data

Baseline data on vital sign measurement and ventilation parameters will be recorded from data already generated in the intensive care unit. These values will be obtained closest to prior to the time of study initiation. Prior to administration of the surfactant a TA sample and EDTA and Transfix blood samples will be obtained from the patient and a chest ultrasound will be performed before and after.

#### Demographic Information

1. Patient demographics
2. Age, gender, ethnicity, height, weight, predicted body weight
3. Clinical frailty score (very fit, Well, managing well, vulnerable, mildly frail, moderately frail, severely frail, very severely frail and terminally ill)
4. Date/time of hospital admission
5. Date/time of ICU admission
6. Date/time of mechanical ventilation
7. List of medications on admission to hospital
8. List of medication on admission to ICU
9. Co-morbidities

- a. Hypertension
- b. Diabetes
- c. Chronic kidney disease
- d. Chronic respiratory diseases (inc. Asthma, COPD)
- e. Chronic cardiac disease
- f. Cardiovascular disease (inc. Stroke/TIA, STEMI/NSTEMI/CABG/Heart failure)
- g. Cancer (active or treatment within a year)
- h. Chronic liver disease (inc. ALD, NASH, cirrhosis, liver failure)
- i. Immunosuppression
- j. Other medical history or co-morbidities

#### APACHE 2 Score at ICU admission

Date/time collected

History severe organ failure or immunocompromise (heart failure class IV, cirrhosis, chronic lung disease, or dialysis dependent) (Yes/No), age, temperature, MAP, pH, heart rate, respiratory rate, sodium, potassium, creatinine, haematocrit, WBC, GCS, PaO2, FiO2 and acute kidney injury (Yes/No/unknown/N/A)

#### SOFA score calculations

Date/time collected

Cardiovascular score, respiratory score, coagulation score, hepatic score, renal score and CNS score

#### Physiology at baseline (closest to prior to study initiation)

1. Pulse, blood pressure, oxygen saturation and body temperature
2. Ventilator setting (date/time of measurements)  
Mode (mandatory, spontaneous, mixed), PEEP, tidal volumes, compliance, mean airway pressure, peak airway pressure, plateau pressure, I: E ratio, respiratory rate, use of nitric oxide, supine or prone
3. Oxygenation  
PaO2, FiO2, oxygen saturations, pH, CO2, lactate
4. Blood markers:  
Haemoglobin, haematocrit, WBC, neutrophil, lymphocyte, eosinophil, platelet, INR, PT, ALT, ALP, bilirubin, AST, sodium, potassium, urea, creatinine, glucose, CRP, PCT, LDH, D-dimer, triglycerides, troponin, ferritin and CK
5. Radiological Markers  
CXR- are infiltrates present? Number of quadrants? and CXR report
6. USS of lungs
7. The need for renal replacement therapy
8. The need for cardiovascular support
9. The use of adjunctive therapies  
(E.g. Antivirals, antibiotics, steroids, list of sedation medications, list of Inotrope/vasopressor medications)

## **7.7 Trial assessments**

### **Vital Signs & Ventilation Parameters**

Pulse, blood pressure, body temperature, oxygen saturations, PaO2, FiO2, PEEP requirements and tidal volumes will be recorded at the time points indicated in the schedule of events (appendix 1). These will be measured constantly whilst the patient is managed by the intensive care team.

Vital signs and ventilation requirements will be recorded at baseline. During surfactant administration, the above vital sign and ventilation parameter measurements will be recorded in between the administration of each vial. Following each dose, these will then be recorded hourly until the administration of the next dose and this will then be repeated. Following administration of the final dose, vital sign and ventilation parameter measurements will be recorded at 30 hours post first dose and then 6 hourly until 48 hours post first dose.

Measurements will then be taken daily during the follow up period.

### **Chest Ultrasound**

A chest ultrasound will be conducted at the time points indicated in the schedule of events (appendix 1). For patients randomised to the treatment arm, a chest ultrasound will also be performed before and after each dose of surfactant. The chest ultrasound will be carried out through use of the Butterfly IQ ultrasound device. Images will be stored in a secure database.

### **Administration of Nebuliser**

The AeroFact-COVID™ (AF-COVID) is an investigational drug/device combination product.

(Details of functioning and dosing are included in section 8 of this Protocol and in the IB and Device Technical File)

### **Infusion of *methyl*-D9-choline chloride**

Deuterated *methyl*-D9-choline chloride will be dissolved in water at 10 mg/ml and infused at a dose of 3 mg/kg body weight over 3 hours, initiated during the stabilization period between intubation and administration of the first dose of surfactant. This timing is chosen to avoid conflict with time-consuming process of surfactant nebulisation. *Methyl*-D9-choline incorporation into lung surfactant dipalmitoyl phosphatidylcholine (DPPC), the major surface-active component, will measure surfactant phospholipid synthesis. It will answer several mechanistic questions. These include:

- 2.) Is surfactant therapy associated with an earlier restoration of surfactant synthesis, indicating recovery?
- 3.) Does the synthesis analysis confirm a reduced number of ATII cells? Can incorporation results provide an estimate of the efficiency of nebulized surfactant delivery to the peripheral lung?

The MHRA have confirmed that *methyl*-D9-choline chloride is not an IMP. A metabolic pathway for *methyl*-D9-choline incorporation into PC is shown below, together with an example of the diagnostic mass spectrometry scans used for detection and quantification of unlabelled and deuterium-labelled PC.

#### Phosphatidylcholine synthesis from deuteriated choline

[figure not shown]

#### Tandem MS/MS scans detect newly synthesised PC 9 mass units greater than unlabelled PC

[figure not shown]

### Sample collection

Samples to be taken for a combination of trial assessment and mechanistic studies are:

#### Blood Sample Collection

EDTA (10 ml) and Transfix (9 ml) blood samples will be taken at 0, 8, 24, 48 and 72 hours (while hospitalised). Blood samples will be collected immediately before administration of the first dose (t=0h), second (t=8h) and third (t=24h) doses of surfactant.

Arterial blood gasses (~1 ml) will be taken at intervals for the clinical trial at 0, 1, 2, 3, 6, 8, 9, 10, 11, 14, 18, 24, 25, 26, 27, 30, 36 hours. Results will be made available to clinicians and will largely replace the requirement for samples to be taken for routine clinical care which would normally require 6-12 blood gasses within 24 hours.

#### Urine pregnancy test

Urine will be tested for  $\beta$  HCG at screening for female volunteers of childbearing potential. As patients will not have the capacity to confirm their medical history in relation to their childbearing potential and this information may not be available in their medical notes, investigator discretion will be used to confirm whether pregnancy testing is required.

#### Closed suction tracheal aspirate samples

TA samples will be taken at 0, 8, 16, 24, 48 and 72 hours. The t=0-hour sample will additionally provide an estimate of baseline surfactant composition and concentration. The subsequent samples will be used for the mechanistic studies outlined above (section 2) and will assess the efficacy of surfactant administration. Baseline TA samples will be collected immediately before administration of the first dose of surfactant (t=0h). Samples will then be collected immediately before the second (t=8h) and third (t=24h) doses of surfactant and at 16, 48 and 72 hours thereafter if the patient is still intubated.

Additional TA samples will be taken for diagnostic PCR for SARS-CoV-2 on Days 3 (72 hrs), 5, 10, 15 and 28 (if still hospitalised).

### 7.8 Long term follow-up assessments

Patients will be monitored constantly as part of their routine clinical care in the intensive care unit. For the purpose of the study, follow up data will be recorded hourly from the administration of the last dose

of surfactant (24 hours) until 32 hours post first dose, 4 hourly until 48 hours post first dose and then daily until day 28, or until the time that the patient is discharged from hospital if this takes place first. A chest ultrasound will be performed daily until this time.

There is no anticipated risk of losing patients to follow up given that they will be hospitalised. Patients may choose to withdraw from the study when they re-gain the capacity to consent for themselves. In these cases, no additional data will be collected. Data can be collected retrospectively by the research team as intensive care records will remain available.

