#### 3.3.2 Secondary Endpoints

The key secondary endpoint is safety over the first 28 days after administration of surfactant assessed by:

1. Cumulative incidence of serious adverse events (SAEs and SADEs);  
Cumulative incidence of Grade 3 and 4 adverse events (AEs)  
Cumulative incidence of ADEs and  
Changes in white cell count, hemoglobin, platelets, creatinine, glucose, total bilirubin, ALT, and AST over time.

Other secondary endpoints are:

2. Change in  $\text{PaO}_2/\text{FiO}_2$  at 24 and 48 hours after study initiation
3. Change in value of Ventilation Index at 24 and 48 hours after study initiation
4. Change in pulmonary compliance ( $\text{L}/\text{cmH}_2\text{O}$ ) at 24 and 48 hours after study initiation

5. Change in PEEP requirement at 24 and 48 hours after study initiation
6. Ordinal outcome assessed daily while hospitalised and on days 15 and 28
  1. *Not hospitalised, no limitations on activities*
  2. *Not hospitalised, limitation on activities;*
  3. *Hospitalised, not requiring supplemental oxygen;*
  4. *Hospitalised, requiring supplemental oxygen;*
  5. *Hospitalised, on non-invasive ventilation or high flow oxygen devices;*
  6. *Hospitalised, on invasive mechanical ventilation or ECMO;*
  7. *Death.*
7. Duration of mechanical ventilation- Number of days on mechanical ventilation
8. Mechanical ventilator free days (VFD) at day 21
9. Length of intensive care unit stay
10. Number of days hospitalised
11. Mortality at day 28 - Date and cause of death (if applicable)

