| 6                           | To evaluate clinical improvement defined by time to one improvement point on an ordinal scale, as described in the WHO master protocol (2020) daily while hospitalised and on days 15 and 28 | 
Ordinal outcome assessed daily while hospitalised and on days 15 and 28 hospitalised
 
1. Not hospitalised, no limitations on activities
 
2. Not hospitalised, limitation on activities;
                                                                                                                             | Assessed daily while hospitalised and on Days 15 and 28.     |

|    |                                              |                                                                                                                                                                                                                                                                  |                                               |
|----|----------------------------------------------|------------------------------------------------------------------------------------------------------------------------------------------------------------------------------------------------------------------------------------------------------------------|-----------------------------------------------|
|    |                                              | 3. Hospitalised, not requiring supplemental oxygen;
4. Hospitalised, requiring supplemental oxygen;
5. Hospitalised, on non-invasive ventilation or high flow oxygen devices;
6. Hospitalised, on invasive mechanical ventilation or ECMO;
7. Death. |                                               |
| 7  | The number of days of mechanical ventilation | Ventilation days                                                                                                                                                                                                                                                 | Every day after study initiation              |
| 8  | Mechanical ventilator free days at day 21    | VFD at day 21                                                                                                                                                                                                                                                    | Every day after study initiation until day 21 |

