| 9  | Length of intensive care unit stay           | ICU length of stay                                                                                                                                                                                                                                               | Every day after study initiation              |
| 9  | The number of days hospitalised              | Hospital days                                                                                                                                                                                                                                                    | Every day after study initiation              |
| 10 | The mortality at Day 28                      | 28-day mortality                                                                                                                                                                                                                                                 | On day 28 after the study initiation          |

| Exploratory Endpoints |                                                                                                                    | Time points                                                                                                                                                                                                                                         |
|-----------------------|--------------------------------------------------------------------------------------------------------------------|-----------------------------------------------------------------------------------------------------------------------------------------------------------------------------------------------------------------------------------------------------|
| 1                     | Tracheal aspirate for viral PCR                                                                                    | Days 3, 5, 10, 15 and 28 while still hospitalised                                                                                                                                                                                                   |

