### **9.9 The type and duration of the follow-up of participants after adverse reactions.**

Patient's that experience an adverse reaction as a result of trial treatment will be followed up until day 28 or discharge from hospital. If additional follow up is required for safety reasons the investigator will discuss this with the participant and make appropriate arrangements. Adverse events will be recorded and reported for the duration of the patient's participation in the study. Any SUSAR will need to be

reported to the Sponsor irrespective of how long after IMP administration the reaction has occurred until resolved.

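### Follow-up recording ends at discharge, but Day 28 mortality and the Day 15 and Day 28 ordinal scores need status after discharge, and the 28-day safety window contradicts the cut-off

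*Protocol*

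**What the plan says.** Section 7.8 sets recording as hourly, then 4-hourly, then daily to Day 28, "or until the time that the patient is discharged from hospital if this takes place first". It adds: "There is no anticipated risk of losing patients to follow up given that they will be hospitalised". The only retrospective source it names is the ICU record: "Data can be collected retrospectively by the research team as intensive care records will remain available". Section 9.9 uses the same limit for patients with an adverse reaction, who "will be followed up until day 28 or discharge from hospital", with more follow-up only where safety calls for it.

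The endpoints are set differently. Section 3.3.2 lists "Ordinal outcome assessed daily while hospitalised and on days 15 and 28". Category 1 of that scale is "Not hospitalised, no limitations on activities"; category 2 is also for patients out of hospital, but with limited activity. The table in section 3.4 times mortality as "On day 28 after the study initiation", and section 3.3.2 also asks for date and cause of death. The key secondary endpoint, safety, covers 28 days.

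Sections 9.2 and 9.4 require adverse events and serious adverse events respectively to be recorded until 28 days after treatment stops, with no exception for discharge.

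**The concern.** Being alive at discharge is not the same as being alive on Day 28, and a hospital chart cannot show whether someone at home is limited in daily activities. If sites stop recording at discharge, two secondary endpoints lose their data source for the patients who recover soonest, and a death after discharge may go unseen. Whether status is known then depends on recovery, so the gap is informative. This is a matter of data collection, which the protocol fixes. A statistical analysis plan cannot restore observations that sites were told not to make, and activity limitation on a particular day is hard to reconstruct later.

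**Working it through.** The protocol states no figure on this point, so there is none to reproduce. The check sets the follow-up rule beside each outcome that needs data up to Day 28.

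| Outcome | Required by | Available after discharge under 7.8 |
|---|---|---|
| Ordinal score, Days 15 and 28 | 3.3.2, 3.4 | Known to have left hospital; category 1 against 2, readmission and death unknown |
| Mortality at Day 28 | 3.3.2, 3.4 | Alive at discharge only |
| Time to one-point improvement | 3.2, 3.4 | Nothing further needed (see below) |
| AEs and SAEs | 3.3.2, 3.4, 9.2, 9.4, Appendix 1 | Required by these passages; cut off by 7.8, and by 9.9 for adverse reactions |
| Co-primary endpoints at 48 hours | 3.3.1 | Not affected |

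**Is there a source elsewhere?** Appendix 1 has no post-discharge visit, telephone call or record check, and no row for the ordinal scale or vital status. Its Day 14 to 28 columns list ventilation parameters and daily chest ultrasound, which suppose an inpatient. The telephone appears only in the assent procedure (section 7.2). Section 9.5 requires deaths during the study to be reported but does not say how a site would learn of one after discharge.

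**Time to improvement.** Patients enter on mechanical ventilation, which is category 6. A one-point gain is reached at category 5 or better, so it has occurred by discharge at the latest and daily in-hospital scoring captures it.

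**Safety window.** The last dose is at 24 hours. 24 hours + 28 days = 29 days, so the window in 9.2 and 9.4 closes at about Day 29.

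**Size for mortality.** Section 4 plans 4 × 3 = 12 treated and 4 × 2 = 8 control patients, 20 in all, matching the planned sample size. If *k* of *n* patients in an arm have unknown vital status at Day 28, the distance between the lowest and highest possible 28-day mortality is *k*/*n*.

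- One treated patient: 1/12 = 8.3 points.
- One control patient: 1/8 = 12.5 points.

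The protocol gives no share discharged before Day 28. Taking 20% to 50% purely as an assumption, and rounding to whole patients:

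- Treated: 2 to 6 patients, 2/12 = 17 to 6/12 = 50 points.
- Control: 2 to 4 patients, 2/8 = 25 to 4/8 = 50 points.

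These are logical bounds with every unknown patient alive at one end and dead at the other. They are not a forecast of bias.

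**The case against.** The discharge clause can be read as governing only the frequency of bedside recording. Where the authors wanted a hospital-only limit on a fixed day they wrote one, as for the Day 15 and Day 28 tracheal aspirate PCR in section 7.7. Section 3.4 has the ordinal outcome "assessed daily while hospitalised and on days 15 and 28", which separates daily from fixed-day scoring, and the trial summary states 28 days of follow-up. A careful site might therefore collect these data anyway. This shows that the endpoints were meant to be complete. It does not supply a procedure, and 7.8 expects no loss to follow-up on the ground that patients are in hospital, directly after allowing for discharge.

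On safety the objection largely stands. Sections 9.2 and 9.4 set the window without regard to discharge, the investigator's responsibilities mention participants who return for follow-up, and Appendix 1 marks adverse event assessment daily to Day 28 without condition. A reader might infer that the protocol abandons safety capture at discharge. It does not; its passages conflict.

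Two other stronger readings also fail. One is that discharged survivors would drop out of the mortality denominator and inflate the rate. Nothing in the protocol excludes them; the likelier result is that they are counted as alive. The other is that everything is missing for the patients who do best. They are known to have left hospital alive; what is unknown is their activity limitation and any later change.

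Finally, this is an exploratory pilot of up to 20 patients with 48-hour co-primary endpoints, and section 8.7 rules out formal comparison of safety between groups. That limits the reach of the point without removing it.

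**Conclusion.** The point holds in a limited form. Day 28 vital status and the fixed-day ordinal scores have no described source after discharge. As written, 28-day mortality becomes in-hospital mortality, and discharged patients cannot be assigned to category 1 or 2 on Days 15 and 28. Sections 7.8 and 9.9 also contradict 9.2, 9.4, the endpoint table and Appendix 1 on safety capture.

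The firm figures are 8.3 points of possible 28-day mortality per treated patient of unknown status and 12.5 per control patient, assuming all four cohorts fill as planned. Any total depends on a discharge rate that the protocol does not give. The co-primary endpoints, the power table and time to one-point improvement are unaffected. The protocol should be amended, but the main analysis is not at risk.

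**What to change.** Amend section 7.8 and Appendix 1 so that every randomised patient who has been discharged before Day 15 or Day 28, and has not withdrawn, has vital status, hospitalisation and activity limitation recorded for that day by telephone or record check (activity limitation will usually need the call). Ask about adverse events and serious adverse events at the same contact. Add rows for the ordinal scale and vital status to Appendix 1, and remove the statement that no loss to follow-up is expected because patients are in hospital.

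Reconcile the discharge cut-off in 7.8 and 9.9 with the existing window in 9.2 and 9.4. Restating that window as ending on Day 28 would slightly shorten it, since it now runs to about Day 29.

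The cost is at most two short contacts per discharged patient, in a trial of up to 20, plus the amended text.
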